##### Outcomes

We estimated based on our prior work with the population that 20% of the sample will not be on ART at baseline and thus would have detectable viral load. The remaining estimated 80% of the enrolled sample would report limited engagement in care as evidenced by low ART adherence or poor appointment attendance. Therefore, we conservatively estimated that at least 40% (and as many as 60%) will have detectable viral load at baseline. Those who meet eligibility criteria were at increased risk of virologic failure resulting from poor engagement in care. If our intervention is successful, a higher proportion of intervention participants will display virologic control relative to control group participants.

Therefore, we hypothesized that, following the intervention, the odds of undetectable viral load will be higher for intervention participants than for control participants (Hypothesis 1). Our primary interest was to estimate the marginal or population-average effect of intervention participation on each outcome rather than the effect for a hypothetical average subject. (93) Moreover, within-subject correlations among outcomes are considered nuisance parameters rather than quantities of interest to be modeled explicitly. Accordingly, generalized estimating equations (GEE) will be used to perform the proposed primary analysis, which is a planned time-averaged comparison of post-baseline measurements across the intervention and control groups to test primary Hypothesis 1. Alpha will be set at 0.05 for this planned comparison. Any additional *post-hoc* comparisons (e.g., paired comparisons of the control and intervention groups at each time point) will maintain a nominal alpha level of 0.05 through the use of simulation-based stepdown multiple comparison methods (94). Reflecting the binary nature of the virologic control outcome, a binomial distribution and logit link will be used for this analysis. Though GEE estimates are consistent even if the correlation structure is misspecified, GEE's statistical efficiency improves as the working correlation structure more closely approximates the actual correlation structure (95). Thus, working correlation structures suitable for the study's design will be considered (e.g., unstructured, AR (1), exchangeable, *M*-dependent) (96). The QIC statistic will be used to select the final working correlation structure (97). Robust Huber-White “sandwich” standard errors will be used to obtain correct inferences even if the chosen correlation structure remains slightly misspecified. GEE case deletion diagnostics (e.g., DFBetas, Cook's *D*) will be used to investigate whether influential cases are present; if such cases are found, results will be reported with and without influential cases included (98). As noted above, standard care quality (SCQ) will be included as a covariate in this analysis. In addition, randomization strata indicators will be included as covariates to obtain unbiased results (99). Additional covariates may be included if they improve QIC.

For the secondary outcome of HIV care engagement, we hypothesized that women assigned to *Healthy Divas* will have higher engagement in HIV care at follow-up than those assigned to the control condition as measured by appointment attendance and ART uptake, adherence and persistence (Hypothesis 2). We will use the same GEE methods described above to explore whether TWH in the *Healthy Divas* intervention group have higher HIV treatment engagement relative to those in the control group.

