#### Eligibility Criteria

Potential participants were considered eligible if they were ≥18 years; assigned male sex at birth but did not currently identify as male; English- or Spanish-speaking; HIV-positive confirmed via antibody testing; and reported suboptimal engagement in HIV care, as indicated by one or more of the following: (a) Not on ART; (b) If on ART, reporting less than perfect adherence on a validated adherence rating scale; or (c) Reporting no HIV primary care appointments in the prior 6 months.

Potential participants were considered ineligible if they exhibited evidence of severe cognitive impairment or active psychosis, as determined by the Project Director in consultation with the Principal Investigator (PI), a licensed clinical psychologist.

Individuals were not excluded if they were actively engaged in substance use. Substance use is prevalent in TWH, and exclusion based on active substance use would have resulted in a sample that does not represent the target population. Informed by our prior work (21), the intervention includes a focus on the role of substance use and alcohol in optimizing engagement in care. However, if an individual was intoxicated at the time of a visit, we rescheduled the session to preserve the integrity of the data collection and intervention delivery.

We considered only enrolling TWH with detectable viremia but opted for inclusion based on indicators of poor engagement instead. This approach allowed the intervention to prevent potential treatment failure in TWH whose patterns of engagement in care put them at risk of poor outcomes. We contended that this was likely to be a more cost-effective long-term approach, as preventing virologic failure may have greater individual and public health benefit than waiting to intervene until treatment failure. It was also more exportable to community settings, thus enhancing external validity; if the intervention demonstrates efficacy, agencies will be able to adopt it with easier screening procedures than if eligibility had been based on clinical parameters such as viral load. From a methodological perspective, this decision allowed more statistical power, as the primary outcome could fluctuate in both directions for the two randomized groups, thereby increasing internal validity. We anticipated that 50% of the sample at baseline would have undetectable viral load.

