### Assignment of Interventions

#### Allocation

##### Sequence Generation

Participants were randomly assigned via stratified randomization with randomly permuted block sizes of 2, 4, and 6. There were eight strata based on site, age <40 years old vs. not, and binary race (Black vs. not for San Francisco and Latina vs. not for Los Angeles) with a 1:1 allocation to either *Healthy Divas* or control condition using a computerized secure and fraud-resistant procedure employed in our team's prior studies. Our experience with over 700 participants in three RCTs has indicated that this method is successful for achieving balance across demographic, mediating, and outcome variables.

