##### Primary Outcome

To determine whether TWH randomized to *Healthy Divas* will achieve or maintain higher rates of undetectable viral load than TWH assigned to a treatment as usual control condition, the primary outcome was assessed. This RCT's primary outcome was virologic control as indicated by an undetectable HIV-1 level (undetectability = < 20 copies/mL). Virologic control was conducted at baseline and at each follow-up assessment for 12 months post-randomization at 3-month intervals. A study phlebotomist performed peripheral venous blood sample collections. This process included: completing laboratory requisitions forms with collection date, time, and other relevant information; preparing two tubes for HIV-RNA; performing venipuncture and blood draw; spinning and freezing each specimen; placing each labelled specimen and requisition form in a shipment bag for pick up. Results were securely accessed through the Care360^TM^ platform in San Francisco and Foundation Laboratory in Los Angeles and entered and saved in a study password-protected Access form.

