#### Statistical Methods

##### Analysis Population and Missing Data

For preliminary analyses and missing data, one-way frequency tables for all variables and measures of central tendency and variability for continuous variables will characterize the sample. These analyses will be stratified by randomization group (i.e., intervention vs. control) to check for imbalances. If the intervention and control groups are found to differ significantly at baseline on one or more covariates (e.g., on ART vs. not), we will use methods based on the Rubin causal model (e.g., propensity scores, targeted maximum likelihood estimation, double-robust estimation) to obtain the desired marginal effect estimates under the counterfactual assumption of balanced groups (82–86). In general, we will address incomplete data multiple imputation (MI) (87) because MI makes the relatively mild assumption that incomplete data arise from a conditionally random (MAR) mechanism rather than the completely random process (MCAR) assumed by *ad hoc* methods such as listwise data deletion (88). Auxiliary variables will be included in analyses involving incomplete data to help meet the MAR assumption (89, 90) and sensitivity analyses will be conducted with pattern-mixture models to assess the robustness of the MAR assumption (91). SAS (92) will be used to perform the proposed analyses.

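### Baseline viral-load status enters the primary GEE only conditionally, by a significance test or by QIC, when it should be a fixed covariate with a standardised marginal effect

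*Protocol article*

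**What the plan says.** All references are to the Protocol article.

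- **Primary model** (Statistical Methods, Outcomes): a logit GEE for "a planned time-averaged comparison of post-baseline measurements across the intervention and control groups to test primary Hypothesis 1". Two covariates are named: "standard care quality (SCQ) will be included as a covariate in this analysis", and "randomization strata indicators will be included as covariates to obtain unbiased results". The stated target is a marginal effect.
- **Strata** (Sequence Generation): "There were eight strata based on site, age <40 years old vs. not, and binary race". Viral load is not among them.
- **Availability of baseline**: "Virologic control was conducted at baseline and at each follow-up assessment for 12 months post-randomization at 3-month intervals" (Primary Outcome). Data Collection Methods places the blood draw before randomization. Eligibility Criteria adds: "We anticipated that 50% of the sample at baseline would have undetectable viral load".
- **First conditional route** (Outcomes): "Additional covariates may be included if they improve QIC".
- **Second conditional route** (Analysis Population and Missing Data): "If the intervention and control groups are found to differ significantly at baseline on one or more covariates (e.g., on ART vs. not"), then propensity-score, TMLE or doubly robust methods will be used.
- **Secondary outcomes**: Trial Design describes the engagement composite as improvement within a participant, but the analysis text carries over the primary GEE methods and names no baseline score.

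**The concern.** Baseline undetectability is the same assay in the same person, so it is likely to predict follow-up status strongly. It also separates participants who must achieve control from those who must maintain it, the two halves of Hypothesis 1. The plan commits to site, age, race and SCQ, and leaves this variable to two data-dependent rules.

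Three things are at stake:

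- precision that costs nothing to obtain;
- a chance imbalance too small to be significant, which moves the unadjusted estimate in that particular trial;
- the meaning of the primary odds ratio, which changes according to whether QIC brings the variable in.

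**Working it through.** **Inputs.** From Sample Size: 114 analysable per arm, four post-baseline measurements, alpha 0.05 (taken as two-sided), power 0.80, rho 0.20–0.80. Also 278 enrolled 1:1, so 139 per arm, and 50% undetectable at baseline (Eligibility Criteria). The baseline-to-follow-up correlation is not given; it is assumed equal to rho, then to rho/2.

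**Step 1: reproduce Table 5.** With exchangeable correlation, the variance factor for the mean of four visits is f = (1 + 3·rho)/4. At rho 0.5, f = 0.625 and h = 2.80·√(2/114 × 0.625) = 0.293, as printed (0.293–0.297). A pooled two-proportion calculation with 114/f per arm returns the odds ratios and differences in the P0 = 0.30 and 0.80 columns to the printed decimal. The column labelled 0.55 is matched within 0.4 points at 0.55, and exactly at P0 = 0.50 (11.6, 14.5 and 16.8 points at rho 0.2, 0.5 and 0.8). No baseline term is needed, so the stated 80% power does not depend on adjustment.

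**Step 2: add baseline.** If baseline correlates rho with each visit, the factor becomes f − rho²; at rho/2 it becomes f − rho²/4. Power at the Table 5 effect is Φ(2.80/√ratio − 1.96).

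| rho | f | f − rho² | ratio | power | power at rho/2 |
|---|---|---|---|---|---|
| 0.2 | 0.400 | 0.360 | 0.90 | 0.84 | 0.81 |
| 0.5 | 0.625 | 0.375 | 0.60 | 0.95 | 0.84 |
| 0.8 | 0.850 | 0.210 | 0.25 | >0.99 | 0.875 |

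At P0 = 0.50 the detectable difference falls from 11.6, 14.5 and 16.8 points to 11.0, 11.3 and 8.5.

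Simulated logistic GEEs (independence working correlation, robust standard errors, 3000 runs) gave smaller gains:

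- P0 = 0.55: 0.82 to 0.84 (rho 0.2), 0.82 to 0.91 (0.5), 0.83 to 0.97 (0.8).
- rho 0.5: 0.80 to 0.89 at P0 = 0.30, and 0.81 to 0.84 at P0 = 0.80.

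**Step 3: imbalance that escapes the trigger.** The standard error of the baseline arm difference is √(2 × 0.25/139) = 6.0 points, so anything up to 1.96 × 6.0 = 11.8 points is non-significant. The chance of a difference above 5 points is about 0.40, and above 10 points about 0.095. The shift in the unadjusted time-averaged difference is about rho × imbalance. At 11.8 points:

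- rho 0.2: 2.4 points, against a detectable 11.6;
- rho 0.5: 5.9 points, against 14.5;
- rho 0.8: 9.4 points, against 16.8.

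**Step 4: the effect measure.** In the simulations at P0 = 0.55, adding baseline status to the logit model moved the mean odds ratio from 1.87 to 2.10 (rho 0.5) and from 2.11 to 3.44 (rho 0.8). The adjusted figure is conditional on baseline status. SCQ and the strata also condition the odds ratio; that amount was not computed.

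**The case against.** The strongest reply is that the plan does provide for adjustment. Significant imbalance triggers causal-model methods, and QIC can admit any covariate. If baseline status is as predictive as supposed, QIC should pick it. A simulation of that rule supports this (114 per arm, 1500 runs per setting, only arm and baseline as terms). At P0 = 0.50 and rho 0.2, 0.5 and 0.7, QIC chose baseline in 99.9%, 100% and 100% of runs, with the same power as always adjusting (0.84, 0.92, 0.98). With follow-up rho 0.2 and baseline correlation 0.1 it was chosen in 75%, but there adjustment moves power only from 0.80 to 0.81.

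This stands against a stronger reading. A reader might infer that baseline imbalance goes uncorrected, or that the trial forfeits the whole power gain. The documents support neither: two routes exist, and the gains above are relative to never adjusting. It does not settle the matter. The QIC rule is permissive and lists no candidates, and entry by that route changes the odds ratio.

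It can also be said that the test is valid as planned. It is: randomization keeps the unadjusted comparison unbiased on average, simulated null rejection was 5.1%, and a one-SD imbalance (6.0 points) shifts the result by only about 3 points at rho 0.5.

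Marginal could be read merely as GEE rather than a subject-specific model. Even so, the size of the primary odds ratio would depend on a covariate choice made after seeing outcomes.

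Lastly, a full covariate list is often left to the SAP, which is not shown. But the article does fix named covariates and a selection rule, and that rule is what is questioned here.

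**Conclusion.** The point holds as one of forgone precision, conditional bias and a primary effect measure left to data-driven choice. It is not a finding of an invalid test or a power shortfall; a reader might infer either, but Table 5 reproduces without any baseline term.

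The size depends on a correlation that the article does not give. If it equals Table 5's rho, power rises from 0.80 to roughly 0.84 (rho 0.2), 0.84–0.95 (rho 0.5, by base rate and method) and 0.97 or more (rho 0.8). At half that correlation the result is about 0.81–0.88. The 5.9-point shift at rho 0.5 is the worst case that escapes the significance trigger, not a typical one, and it assumes 50% prevalence and a follow-up-on-baseline slope of rho.

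**What to change.** State in the SAP that baseline undetectability (yes/no) is a fixed covariate in the primary GEE, whatever the baseline significance tests or QIC show. Standardise the fitted model over the observed covariates (g-computation) and report the marginal odds ratio and risk difference, so that the stated target is kept. In a simulation at P0 = 0.50 with 111 per arm, the standardised risk difference kept the full power gain with an unchanged mean estimate. Include the baseline value of each score in the Hypothesis 2 and 3 models.

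The cost is a few sentences of SAP wording and a standardisation step; the data are already collected. Participant Timeline says analyses were starting at submission. If treatment effects have already been estimated, report this as a labelled sensitivity analysis beside the planned one.

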##### Additional Analyses

To explore the effect of the intervention on hypothesized mechanisms of action, secondary analyses will use GEE to evaluate whether TWH assigned to the intervention report higher post-intervention mean scores on theory-based constructs such as health care empowerment, gender affirmation, adherence self-efficacy, social support, HIV treatment information, and treatment beliefs and expectancies (Hypothesis 3). These analyses will also investigate whether these constructs mediate the relationship between intervention group assignment and virologic control. Statistical mediation will be assessed using the causal inference-based approach of Valeri and VanderWeele, which yields optimal estimates of indirect effects in the presence of binary outcomes and moderator-mediator interactions (100). In these analyses mediators will always temporally precede outcomes to uphold temporal ordering assumptions. For instance, mediators at 3 months will be considered for analyses involving virologic control at 9 months and mediators at 9 months will be considered for analyses involving virologic control measured at 12 months.

### Monitoring

#### Data Monitoring

Recruitment goals, missing data, and follow-up failures were monitored monthly throughout the trial.

##### Formal Committee

The study's data and safety monitoring board (DSMB), the “University of California, Los Angeles (UCLA) DSMB for Addiction Medicine,” is independent from the sponsor; members do not have any competing interests. Board members were chosen for their relevant expertise on study content, target populations, and methodologies. The roles of our DSMB include: reviewing analyses of outcome data and data safety to determine whether the trial should continue as originally designed, should be changed, or should be terminated based on these data; reviewing trial performance information, such as accrual information; determining whether and to whom results should be released prior to the reporting of the study results; reviewing reports of related studies to determine whether the monitored study needs to be changed or terminated; reviewing major proposed modifications to the study prior to their implementation; and providing study leadership with written summary information following board meetings.

##### Interim Analysis

No interim analyses took place during the trial.

#### Harms

All safety-related risks of harm were monitored routinely at the time of the assessment or intervention session. The security of confidential information was monitored regularly. Study staff were trained in asking questions about sensitive topics in a caring and non-threatening manner and stopping questioning at the first sign of discomfort or on request. Privacy, confidentiality, and disclosure comfort were emphasized in every session. All participants were reminded that they were not required to disclose their HIV status (or any other personal information) to anyone at any time. Group facilitators requested that participants agree to respect the privacy and confidentiality of other members of the group and to not disclose anyone's personal information to anyone outside of the group. Participants were informed that assessment responses are kept confidential and are not used against them in any manner, including for reasons of legal action or medical treatment. Study staff were trained to identify a participant who reports distress. For participants who report distress or suicidality, a protocol guided staff action, including steps to assess the level of distress, to obtain emergency contact information for clinical supervisors, and to obtain up-to-date phone numbers for crisis centers, hotlines, and referral agencies.

Study staff were trained to report breach of confidentiality risks incurred by participants to the Project Director, who in turn was trained to inform the PI. Any participant in need of treatment due to distress was referred for appropriate services after staff followed the participant distress protocol and informed the Project Director and PI. Finally, the PI was responsible for informing the DSMB chair, IRB through the IRB adverse event reporting procedure, and the sponsor Project Officer through immediate email of any life-threatening incidents and through annual reports of other incidents. The PI was prepared to take appropriate action to stop the study, release a participant from the study, or modify procedures to reduce and/or eliminate the abovementioned risks if they occurred at an unacceptable level.

#### Auditing

No trial audits were planned or conducted, but participating institutions had the authority to perform random audits of research protocols.

## Discussion

The *Healthy Divas* intervention and corresponding RCT protocols were developed with extensive formative work, including input from TWH, providers, and other community stakeholders. The forthcoming results will represent a critical step in the development of an intervention that specifically addresses the unique and wide-ranging challenges experienced by TWH, a group whose disproportionate rates of HIV infection and poor outcomes warrant focused efforts. This work fills a significant public health gap through the evaluation of a theory-driven, piloted, culturally tailored intervention to improve engagement in HIV care among TWH. The project was established within two novel and complementary theoretical models developed by the investigative team; the Model of Gender Affirmation and the Health Care Empowerment Model offered a rich foundation on which to build the *Healthy Divas* intervention. We also implemented a behavioral composite of engagement in HIV care scale, which is supported by preliminary data and offers clear direction for promoting greater engagement in HIV. This RCT tested an innovative engagement in HIV care intervention designed specifically for TWH. It, therefore, potentially represents an important contribution in providing an evidence-based approach to improving HIV clinical outcomes among this population at heightened risk for treatment failure and onward transmission of HIV. In addition to the individual-level intervention described here, structural interventions are urgently necessary to improve HIV care outcomes among TWH (101).

Although the results of this RCT are not yet available, the *Healthy Divas* intervention is already being replicated in three US cities: Birmingham, Alabama; Newark, New Jersey; and Oakland, California. Funded by the Health Resources and Services Administration (HRSA) / HIV/AIDS Bureau (HAB) Ryan White HIV/AIDS Program (U69HA31067; U90HA31099), *Healthy Divas* is being implemented for 4 years (August 2017–July 2021). We attribute this early replication to the urgent need for effective gender affirming and transgender-specific peer led interventions focused on HIV treatment engagement and outcomes among TWH. We anticipate that the results from this RCT will have the potential to transform gender-affirming HIV health care for a population at dramatically elevated risk for disparately negative personal and public health outcomes.

